#### Outcome measurement

2.1.6

The visual analogue score is done by drawing a straight line on a piece of white paper, with one end representing a score of 0 and 1 end representing a score of 10, and allowing the patient to choose a score based on their subjective feelings. Zero means the patient is not in any pain; below 3, indicates moderate pain; 4 to 6, more significant pain; and 7 to 10, very severe and unbearable pain.^[13]^

The Neck Disability Index score is commonly used in clinical practice to evaluate the functional status of the cervical spine. The scale includes 10 areas of pain, personal care, lifting, reading, headache, concentration, work, driving, sleep and recreation. Each item is scored out of 5, with the total score ranging from 0 (no impairment) to 50 (complete paralysis), the higher the score the greater the dysfunction.^[14]^

The surface electromyography (SMEG) was used to inspect the neck muscles of the 3 groups of patients, and the room temperature was controlled at about 24°C and the air humidity was 70% to 80%. The patient's neck skin was first disinfected with 75% of alcohol and the hair was removed with sandpaper to reduce resistance. A carbon pen was used to mark the placement of electrodes on the bilateral neck surface symmetrically.^[15]^ The SMEG signals of the upper trapezius muscle during 20 seconds of maximal voluntary contraction were used and analyzed for frequency domain indices. The patient was placed in a sitting position with his shoulders relaxed and leaning down naturally. Two nonelastic band loops were adjusted to fit over the patient's relaxed shoulders without any constraint, and the patient was made to shrug his shoulders as hard as he can.^[16]^ The sternocleidomastoid electrodes are positioned as follows^[15]^: 1 cm from the midpoint of the line between the mastoid and the sternal head, 2 surface electrodes are placed symmetrically parallel to the direction of the muscle fibers. The patient is asked to lie prone on the operating bed, with the head dangling out of the bed and both heads on either side of the body, while the patient's upper body is fastened with a nylon strap. When the patient is unable to retain the neck extension position and the weight falls to the ground, the examination ends and the duration of posterior neck extensions is recorded. SMEG data from patients during maximal isometric contractions were collected using a ME6000-T8 SMEG in all 3 groups, and then the Mega Win 3.1 software was assigned to process the data. The main analysis indexes used were mean power frequency and median frequency, which are usually closely related to the functional state of the muscle (ie, the degree of fatigue).

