## Abstract

Neurogenic cervical spondylosis is the most common type of cervical spondylosis, accounting for approximately 60% percent of the incidence of cervical spondylosis. Cervical spine Long manipulation and sling exercise training (SET) have obtained good therapeutic results in clinical rehabilitation. The aim of this study was to evaluate the effect of Long manipulation combined with SET on neurogenic cervical spondylosis. In this assessor-blind, randomized controlled trial, 90 eligible patients will be randomized into a combination treatment group (Long manipulation combined with SET), a Long manipulation group and a conventional massage group. The visual analogue score, the Neck Disability Index score, and muscle fatigue in the bilateral upper oblique and Musculus sternocleidomastoideus, using mean power frequency and median frequency from the surface electromyography frequency domain index, will be assessed before and after the intervention at 0 and 4 weeks, respectively.

**Trial registration:** Registered in the Chinese Clinical Trial Registration Center with the number ChiCTR2100054978. Registered December 30, 2021.

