The combined treatment group combines SET on the basis of the Long manipulation group, in which the procedure for Long manipulation is the same as above and the treatment for SET is shown as follow^[12]^: before the start of the treatment look for weak chains, determine the stability and muscle tension of the neck muscle groups and assess the muscle strength of the flexor muscle groups on both sides of the collar to develop a training protocol. Active exercise: the patient is placed in a supine position with slightly flexed knees, the thoracic spine and pelvis are immobilized with elastic cords and the head is secured with a central parting band. The patient is asked to flex the left side, flex the right side, flex the front, expand the back and rotate the neck to the maximum degree and hold for 5 seconds; each dimension is done 5 times and counted as 1 set, a total of 5 sets are completed with 30 seconds rest between sets. Slow, controlled, stable, and pain-free movements of 30 minutes, 5 times/wk for 4 weeks; The study protocol was designed in accordance with the recommendations of the standard program project: intervention trials recommendations 2013 statement. (Table 1; Additional File 2)

**Table 1 T1:** Standard protocol items: recommendations for intervention trials (SPIRIT) figure of the Long manipulation study protocol.

	Time	
Contents	0 wk	4 wk
Screening participants	×	
Sign informed consent	×	
Randomized	×	
Interventions		
Combine treatment group	×	×
Long manipulation group	×	×
Control group	×	×
Evaluation of therapeutic effect:		
VAS score	×	×
NDI score	×	×
SMEG assessment:		
MPF and PF of the bilateral superior	×	×
Oblique and sternocleidomastoid muscles	×	×

MPF = mean power frequency, NDI = Neck Disability Index, SMEG = surface electromyography, VAS = visual analogue score.

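### The only task described after sternocleidomastoid electrode placement is a prone neck-extension hold to failure, which conflicts with the statement that the SMEG data come from maximal isometric contractions

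*Protocol article*

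**What the plan says.** Muscle fatigue stands beside pain and cervical function in the study aim (Method/design). The Abstract defines it through mean power frequency (MPF) and median frequency (MF), measured at 0 and 4 weeks, as "muscle fatigue in the bilateral upper oblique and Musculus sternocleidomastoideus".

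Section 2.1.6 (Outcome measurement) then describes two set-ups.

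- **Upper trapezius.** "The SMEG signals of the upper trapezius muscle during 20 seconds of maximal voluntary contraction were used". The patient sits with loops over the shoulders, and "the patient was made to shrug his shoulders as hard as he can".
- **Sternocleidomastoid.** The electrodes lie close to the midpoint between the mastoid and the sternal head. The text goes straight on: "The patient is asked to lie prone on the operating bed, with the head dangling out of the bed". The test is open-ended: "When the patient is unable to retain the neck extension position and the weight falls to the ground, the examination ends". The quantity noted from it is how long the extension was held.

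The section then says of all three groups: "SMEG data from patients during maximal isometric contractions were collected". It names MPF and MF as the main indices and links them to the degree of fatigue.

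Table 1 (in 2.1.4, Intervention) lists the measures over two rows, "MPF and PF of the bilateral superior" and "Oblique and sternocleidomastoid muscles".

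**The concern.** The electrodes are on one muscle and the task that follows is built around others. The article itself calls the task neck extension and refers to the posterior neck. The sternocleidomastoid is an anterior muscle that acts mainly as a flexor and rotator. Holding the head up in prone is chiefly the work of the posterior extensors. No flexion, rotation or other task that would load the sternocleidomastoid is described.

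The section also disagrees with itself about the type of contraction. A position held until it fails, and scored by time, is not the maximal isometric contraction from which the signal is said to come.

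At stake is whether the sternocleidomastoid half of the fatigue outcome can be interpreted. A reader following the text would obtain those values either from an extensor endurance test of patient-dependent length or from a contraction the article does not describe.

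**Working it through.** The article gives no figure on this point to reproduce. The check is a count and a side-by-side reading.

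**Count of SMEG values per visit.** Inputs: 2 indices (MPF, MF), 2 muscles and 2 sides, from the Abstract and 2.1.6.

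- All values: 2 × 2 × 2 = 8.
- Sternocleidomastoid only: 2 indices × 1 muscle × 2 sides = 4, that is 4 of 8.

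**The two recordings compared (2.1.6).**

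| Feature | Upper trapezius | Sternocleidomastoid |
|---|---|---|
| Task described | Seated shoulder shrug | Prone hold of neck extension |
| Does the task load the muscle? | Yes | Not mainly; it loads the posterior extensors |
| Effort | Maximal | Sustained until failure |
| Length | 20 seconds, fixed | Until the position fails |
| Quantity noted from the task | Frequency-domain indices | Duration of the hold |

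**The two possible readings.**

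1. *The signal is taken during the hold.* The statement about maximal isometric contractions is then wrong for this muscle, and the task does not suit the electrodes. If the whole hold is analysed, the length of the recording depends on endurance. The article itself ties MPF and MF to fatigue, so a patient who lasts longer at week 4 than at week 0 is measured over a different stretch of a fatiguing effort. A treatment that improves endurance would alter the window in which its own effect is read.
2. *The signal is taken during a separate maximal contraction.* The statement is then right, but that contraction is not described, and the hold is a separate test. Its duration is not listed as an outcome in the Abstract or in Table 1.

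Both readings require a correction to the text. Only the first makes the four values invalid as a measure of the named muscle. A further gap is that the weight whose fall ends the test is not introduced anywhere before it.

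**Names.** The Abstract and Table 1 name an upper or superior oblique muscle, whereas 2.1.6 records upper trapezius. Table 1 also abbreviates the second index as PF, whereas the Abstract and 2.1.6 use median frequency.

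**The case against.** The strongest reply is that the article never says the sternocleidomastoid signal is recorded during the hold. The only quantity attached to the hold is its duration, and the following sentence places the SMEG data in maximal contractions. On that reading the hold is a separate endurance test and the real contraction has been left to a fuller document or to the cited methods. This stands in part: the invalidity of the four values and the variable recording length are conditional on the first reading. It does not remove the point. The problem is not only that a detail is absent. The section states one procedure and then contradicts it.

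A reader might infer three stronger things that the article does not support.

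- *That all eight values are compromised, because the other muscle is misnamed.* The seated shrug makes it clear that upper trapezius is recorded. The oblique label is probably a translation slip, and correcting it changes no recording.
- *That the plan analyses the level of MPF and MF where a decline within the contraction is needed.* The article names the indices but does not say whether a level, a slope or a normalised value is derived. That detail may properly sit in the full protocol or analysis plan.
- *That half of the SMEG data certainly fails to measure its muscle.* That requires the hold to be the recording task, which is likely from the order of the text but not stated.

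**Conclusion.** The point holds as a contradiction within 2.1.6 that should be resolved. The prone hold to failure and the maximal isometric contraction cannot both describe the sternocleidomastoid recording. If the hold is the recording task, 4 of the 8 SMEG values would not validly reflect fatigue of the named muscle. Their recording length could also vary with endurance, against a fixed 20 seconds for upper trapezius. Assessor blinding and randomisation would not repair this, because the problem is what is measured, not who measures it or how patients are allocated.

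The conclusion rests on three assumptions: that the order of the text links the hold to the sternocleidomastoid electrodes; the general anatomical view that prone extension mainly loads the posterior neck; and, for the variable length, that the analysed window follows the hold. The trapezius recording, VAS and NDI are not affected. The mismatch in muscle name is a wording correction only.

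**What to change.** Reconcile the statements in 2.1.6:

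1. Record sternocleidomastoid MPF and MF in a maximal isometric contraction that loads that muscle, for example resisted neck flexion, over a fixed window matching the 20 seconds used for upper trapezius. State posture, resistance and window.
2. If the prone hold stays, report its duration separately as extensor endurance and say what the weight is.
3. If the hold is to remain the recording task, drop the claim that these values show sternocleidomastoid fatigue.
4. Name upper trapezius in the Abstract and Table 1 if that is the muscle recorded, and use one abbreviation for median frequency.

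The cost is a small amendment to the measurement procedure, with no extra visit and no extra patients. The article describes no set-up for resisted flexion, so one would have to be specified, and the investigators must judge its suitability for these patients. Patients already measured under the existing procedure need separate handling: week-0 and week-4 values from different tasks should not be compared within a patient, and values from the two procedures should not be pooled. If a maximal sternocleidomastoid contraction is already in use, the change is to the text alone.

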#### Assess safety

2.1.7

To maintain the safety of the subjects participating in this study, the project leader will supervise the data collection process. During each monitoring session subjects will be asked to remain in hospital for 30 minutes after treatment and will be asked if there are any possible signs of discomfort during the trial. Side effects following the intervention will be recorded during each treatment session.

### Data analysis

2.2

#### Sample size calculation

2.2.1

The study used G∗Power version 3.1 software for sample estimation and selected the F-test, which was calculated using the MANOVA model.^[17]^ Effect size = 0.30, α=0.05, power = 0.92, group size 3 and number of repeated measures of 2 were selected to generate a sample size of 81. Taking into account a possible attrition rate of 11% during the trial, the final sample size was obtained as 90 and was allocated in a ratio of 1:1:1, that is, 30 cases in each group.

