## Method/design

2

The study was an assessor-blind, single-center randomized controlled trial. The aim of this study is to investigate the effect of SET combined with Long manipulation on pain, cervical function and muscle fatigue in patients with CRS. The project leader will be responsible for the overall project and will initiate the establishment of the subject project team. The subject project team will be responsible for subject security, recruitment and treatment and assessment, and quality control. The coordinating center staff will be responsible for communication of protocol changes and provision of information. The trial will have a 4-week period. After randomization, subjects will conduct assessments of primary and secondary indicators in 2 phases at 0 and 4 weeks (Fig. 1; Additional File 1).

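### The 92% power at N = 81 names no tested effect, effect-size metric or correlation, and on the repeated-measures MANOVA option that returns 81 it holds only if weeks 0 and 4 are almost uncorrelated

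*Protocol article*

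**What the plan says.** Section 2.2.1 (Sample size calculation) of the protocol article says that the authors used G*Power 3.1 and "selected the F-test, which was calculated using the MANOVA model". The inputs listed are "Effect size = 0.30" and alpha 0.05, followed by "power = 0.92, group size 3 and number of repeated measures of 2 were selected to generate a sample size of 81". The next sentence reads "Taking into account a possible attrition rate of 11% during the trial, the final sample size was obtained as 90", with 30 patients per arm.

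Section 2 (Method/design) fixes the two measurements: "assessments of primary and secondary indicators in 2 phases at 0 and 4 weeks". Section 2.2.2 (Statistical analysis) names MANOVA for the comparisons between groups.

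Three inputs that determine the answer are not given: whether the between-groups, within (time) or group-by-time effect was powered; whether 0.30 is f, f(V) or f²(V); and the correlation between the two visits.

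**The concern.** In repeated-measures power calculations the correlation between visits drives the result, and its direction depends on the effect tested. A higher correlation lowers power for a between-groups test of the visit average and raises it for a univariate group-by-time test. A figure quoted without the effect, the metric and the correlation cannot be interpreted. If it reproduces only at a correlation near zero, it does not describe the trial that will be run.

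The two visits also have different roles. Week 0 precedes treatment, so randomised arms differ there only by chance. A test of the average of weeks 0 and 4 therefore dilutes whatever difference arises by week 4.

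What is at stake is how a null result is read. Under a 92% power label, a non-significant comparison would be taken as fair evidence of no benefit. That reading is not earned if power for the planned comparison is well below 92%.

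**Working it through.** **Inputs from the protocol article, section 2.2.1:** k = 3 groups, m = 2 measurements, effect size 0.30, alpha 0.05, target power 0.92, N = 81, attrition 11%, final N = 90. **Assumed, because not stated:** the correlation ρ between weeks 0 and 4, shown from 0 to 0.7.

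**Method.** Power is the probability that a noncentral F with noncentrality λ exceeds the 5% critical value. For 2 and N − 3 = 78 degrees of freedom that critical value is 3.114.

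**Step 1. Reproduce the stated figure.** MANOVA repeated measures, between factors: λ = f²·N·m / (1 + (m − 1)ρ). At ρ = 0 and N = 81, λ = 0.09 × 81 × 2 = 14.58 and power is 0.928. The first N to reach 0.92 is 79, which becomes 81 when balanced over three arms. The stated N is reproduced.

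**Step 2. Vary the correlation in the same option.**

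| ρ | λ at N = 81 | Power at N = 81 | Balanced N for 92% |
|---|---|---|---|
| 0 | 14.58 | 0.928 | 81 |
| 0.03 | 14.16 | 0.921 | 81 |
| 0.1 | 13.25 | 0.902 | 87 |
| 0.3 | 11.22 | 0.845 | 102 |
| 0.5 | 9.72 | 0.787 | 117 |
| 0.7 | 8.58 | 0.732 | 132 |

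A balanced N of 81 is returned only up to ρ of about 0.03.

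**Step 3. What 0.30 means in that option.** It refers to the average of the two visits. With no arm difference at week 0, the averaged effect is half the week-4 effect, so f = 0.30 on the average needs f = 0.60 at week 4. Conversely, if f = 0.30 were the week-4 effect, the averaged f would be 0.15, λ would fall to a quarter (3.65 at ρ = 0), and power at N = 81 would be 37% at ρ = 0 and 26% at ρ = 0.5.

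**Step 4. MANOVA group-by-time interaction.** λ = f(V)²·N, with no correlation input. At f(V) = 0.30 and N = 81, λ = 0.09 × 81 = 7.29 and power is 0.656. With all 90 patients it is 0.707. Reaching 92% needs N = 154, or 156 balanced. At N = 81, f(V) = 0.42 gives λ = 0.1764 × 81 = 14.29 and power 0.923.

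**Step 5. Univariate group-by-time interaction.** λ = f²·N·m / (1 − ρ). At ρ = 0 this also gives λ = 14.58, hence 81. At N = 81, power rises to 0.985 at ρ = 0.3 and 0.999 at ρ = 0.5, where a balanced 42 would suffice. Here too f = 0.30 implies f = 0.60 at week 4. For three equally spaced arms, f = (adjacent difference) × √(2/3), so the adjacent difference is 0.60 / 0.816 = 0.73 SD and the extreme arms differ by about 1.5 SD.

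**Step 6. Other MANOVA readings.** Global MANOVA with two responses needs 30 patients at f²(V) = 0.30 and 96 (balanced) at f²(V) = 0.09; neither is 81. The within (time) test needs 66 at ρ = 0 and fewer as ρ rises, and it does not compare groups.

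**Step 7. Combined versus Long manipulation.** If f = 0.30 at week 4 and the arms are equally spaced, adjacent arms differ by 0.30 / 0.816 = 0.37 SD. With 27 per arm a two-sided 5% t-test has noncentrality 0.367 × √13.5 = 1.35 and power of about 26%. With f = 0.60 at week 4 the same contrast has about 75%.

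**Step 8. Attrition.** 81 / 0.89 = 91.01, so 92 patients are needed to keep 81 after 11% loss. The stated 90 matches 81 × 1.11 = 89.9. Starting from 90, 11% loss leaves 90 × 0.89 = 80.1, and 81 / 90 = 0.90 corresponds to 10% loss. At ρ = 0, N = 80 still gives 0.925.

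**The case against.** The strongest reply is that the figure reproduces. The listed inputs give 81 exactly, and a journal article may leave the option name and the correlation to a fuller protocol. This stands in part: the N is not miscalculated, and the defect lies in inputs that are unstated. But the paragraph lists its other inputs and quotes a definite power, and on the between-factors option that power needs a correlation close to zero.

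The second reply is that underpowering depends on the reading. On either reading that yields 81, f = 0.30 corresponds to f = 0.60 at week 4. For an effect that large, a simple week-4 comparison of 81 patients has power of about 99.9% (λ = 0.36 × 81 = 29.16), and a univariate group-by-time test has at least 92% at any non-negative correlation. This also stands. A reader might infer from Step 4 that the trial's true power is 66%. The documents do not support that, because 66% requires 0.30 to be f(V), or f at week 4 in an unadjusted comparison, and the metric is not stated. The reply does not rescue the 92%, however. The univariate f is not the metric of the MANOVA interaction, it too returns 81 only at zero correlation, and the protocol article gives no justification for a difference of about 1.5 SD between extreme arms.

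A reader might also infer that the trial has only 26% power for its main question. That goes too far. The stated aim concerns the combination, and no section singles out Combined versus Long as the deciding contrast. The 26% also assumes f = 0.30 at week 4 and equal spacing.

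Finally, the attrition slip is minor: one patient, with almost no effect on power.

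**Conclusion.** The concern holds in a limited form. The 92% at N = 81 cannot be relied on as written, because the tested effect, the effect-size metric and the correlation are all unidentified. On the repeated-measures MANOVA between-factors option, which reproduces 81, the claim needs a week 0 to week 4 correlation of no more than about 0.03. Over an assumed 0.3 to 0.7, power at 81 is 85% to 73%, for a test that averages in a pre-treatment visit. For MANOVA group-by-time at f(V) = 0.30 it is 66%. Only the univariate interaction metric keeps power at or above 92%, and it does so by presupposing f = 0.60 at week 4.

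The correlation range is my assumption, since the documents give none; that scores from the same patient four weeks apart are correlated above 0.03 is a judgement, though a safe one. Underpowering follows under the between-factors reading at such correlations and under the f(V) reading, not under every reading. The attrition arithmetic is wrong by a small amount and does not change the conclusion.

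**What to change.** Keep 90 patients and rewrite the sample size paragraph:

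- Name the G*Power option, the effect tested, the metric of the 0.30 and the correlation entered.
- Replace the single 92% with the power of the group comparison that will actually be made, over a stated correlation range where the test depends on it. For example: with 81 evaluable patients, the MANOVA group-by-time test has 66% power at f(V) = 0.30 and 92% at about f(V) = 0.42.
- If the univariate interaction metric was meant, say so, and state and justify the week-4 difference it implies.
- Label any figure for Combined versus Long (about 26% with 27 per arm) as conditional on f = 0.30 at week 4 and equally spaced arms.
- Correct the attrition sentence: either 11% loss from 90 leaves 80 evaluable, or 90 allows 10% loss to keep 81. Choose according to the loss actually expected, not to fit the number.

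The cost is one reworded paragraph and probably a less favourable stated power. No extra patients are needed.
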